## Abstract

**Background:**

The focus of care has shifted from institutional care to home care. Family caregivers provide the majority of home care that allows an opportunity for their care recipients to live at home and avoid costly institutional care. The aim of this study is to describe the nutritional status, oral health, and quality of life of family caregivers over the age of 65 and their care recipients, and to evaluate the impact of individually tailored diet and oral health advice to their nutritional status and oral health.

**Methods/design:**

Altogether, 250 family caregivers aged 65 or over, and their care recipients are studied in this prospective randomized population-based multidisciplinary 6-month intervention study. Participants are randomly allocated to the intervention groups or the control group. Data collection is performed at three time-points: at baseline and 6 months and after a 6-month follow-up at 12 months. Caregivers’ and their care recipients’ nutritional and oral health status as a primary outcome, and functional ability, cognitive status, quality of life, depression symptoms, sense of coherence, morbidity, and medication of family caregivers as secondary outcomes will be measured using validated self-administered questionnaires and clinical examinations.

**Discussion:**

To our knowledge, this is the first experiment to determine whether caregivers and their care recipients benefit from individual nutritional intervention and oral health intervention in terms of nutrition status, oral health status, and quality of life.

**Trial registration:**

ClinicalTrials.gov NCT04003493. Registered on June 28, 2019

## Background

Family caregivers (FCs) take the main responsibility of home care of older people. Family care is currently a common way to organize care of older people even when care recipients’ (CRs) cognitive and functional abilities are severely decreased. FCs are most often spouses in pensionable age with their underlying illnesses [1]. To support FCs, some countries have implemented various forms of formal support, including monetary support and supply of services. Such formal support provided by municipalities can include financial support for Fcs, services, respite care and counseling, and training. In Finland, home care is supported by care’s allowance that includes allowance fees, necessary services for care recipient, leave for FC (3 days per month), and informal care support services [2]. In Finland, 2018, over 47,500 FCs were granted care allowance, of them 65 years or older were 27,591 [3]. Typically, family care is the round-the-clock responsibility of CR covering all basic and instrumental needs. Intensive caregiving correlates with a greater caregiving burden [4] which may affect nutritional and adequate nutrition intake of FCs themselves and impaired capability to prepare nutritional meals for care recipient [5]. Besides, some FCs already suffer from depressive symptoms and psychological stress [6] and significantly lower quality of life at the start of home care [1].

If the nutrition and oral health statuses of family caregivers are not good, older people’s functional ability and general health can decline. This endangers living at home. Therefore, the nationwide goal of shifting the focus of services to outpatient care will not succeed. To achieve this goal, research is needed; for example, how to care for and improve oral health and nutrition for FCs and how these affect their wellbeing, performance, and quality of life. Caring for older people is considered the most economically and humanly sustainable alternative older people care as the number of older people increases, and social services are reduced. The Ministry of Social Affairs and Health in Finland has also stated that the well-being and rehabilitation of FCs should be developed, and for this purpose, a study on the current situation is needed.

There are few studies on the nutritional status of FCs and care recipients and their relationship to each other. In one study, only 37% of dementia FCs 18% of their care recipients had a normal nutritional status (Mini Nutritional Assessment MNA> 24) [7]. Tombini et al. found that only 4% of patients with Alzheimer’s disease and 35% of their caregivers had normal nutritional status (MNA> 24) [4]. A Finnish study has found that elderly male caregivers (52%), and their care recipients with Alzheimer’s disease are at a greater risk of malnutrition than female caregivers (40%) and their care recipients [8]. There are no studies on the effect of individual tailored nutritional counseling on caregivers’ nutritional status. However, individual nutritional counseling given to older people in home care has been found to have a positive effect on nutritional status [9]. Aims of this study are [1] to describe the nutritional status, nutrients intake, oral health and oral care, and quality of life of FCs and their CRs aged 65 years or older and [2] to evaluate the effect of individually tailored dietary and oral health counseling on the nutritional status, oral health, functional status, and quality of life among FCs and their CRs and [3] to develop an operating model to maintain good nutrition and oral health in FCs.

## Methods

### Study design

This study is a prospective randomized population-based multidisciplinary intervention study. The study design is illustrated in Fig. 1. Participants are randomly allocated to the intervention group or the control group. Primary and secondary outcome measures are assessed at baseline and are repeated at the end of the 6-month intervention and 12 months after a 6-month follow-up. The trial was registered in the ClinicalTrials.gov Registry (NCT04003493), and the study plan was approved by the Research Ethics Committee of the Northern Savo Hospital District (Finland). The study is funded by a grant from the Sirkka and Jorma Turunen Foundation Finland. All participants are providing written informed consent before commencing the study. Participants may withdraw from participation at any time.

**Fig. 1 Fig1:**
[figure not shown]
Flow chart of the study

### Study population

Altogether, 250 FCs (Fig. 1) aged 65 years or over, and 250 CRs living in two areas in Eastern Finland will be recruited in this study. The researcher will record the participants, who will be willing to participate in the study and generate the allocation with the computer to assign participants to intervention. Due to the nature of the study, i.e., intervention on nutrition and oral health, blinding is not possible. So, participants and researchers are not blinded because it is impossible considering the design of the study. The FCs who have a caregiver’s allowance granted by municipalities valid on January 1, 2019, are included in the study.

The service managers for older people in Kuopio and Vesanto contact the caregivers first. They inform FCs about the study and ask them to indicate their willingness to participate in the study. Thereafter, the contact details of those interested are communicated to the researchers who are in contact with the volunteers by telephone. After that, they are receiving comprehensive oral and written information about the study and a consent form.

The sample size is based on power calculations on the main evaluation criteria of the intervention, the nutritional status (P-Alb), and the oral hygiene (plaque amount). In this study, power calculation showed that each subgroup required 60 subjects to achieve a statistical power of 0.80 with *α* of 0.05.

At the baseline, all the participants are interviewed and examined at home by a trained nurse, a clinical nutritionist, and a dental hygienist. Nutrition and oral health are measured at the baseline, at 6 months and 12 months. We have no exclusion criteria regarding maximum age, morbidity, or cognition. Subjects with end-of-life care are excluded. If a CR is unable to reply (e.g., in cases of severe cognitive impairment), data collection will be supplemented with an interview of her/his FC.

The control group does not receive the intervention, but they are guided to the health care, if their health status required it or they were at risk of malnutrition or if they need urgent dental care. If a participant is receiving concomitant treatment for, e.g., Alzheimer’s disease, Parkinson’s disease, diabetes, or cardiovascular disease, it will also be continued during the study.

The participants are encouraged to stay in the study from the beginning. In addition, all measurements are performed at home, giving the participants a better opportunity to participate in the study.

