### Outcome variables

#### Interview and clinical examination by a clinical nutritionist

Nutritional screening is assessed with the MNA test [10]. The MNA is a widely used and validated tool for detecting malnutrition and its risk in older people. It involves a general assessment of health (questions regarding lifestyle, mobility, and drugs), a dietary assessment (questions regarding type and number of meals), anthropometric measurements, and a subjective self-assessment by the patient. The maximum sum score is 30.0; scores of 24.0–30.0 indicate normal nutritional status, scores of 17.0−23.5 a risk of malnutrition, and scores 0−16.5 malnutrition.

Bodyweight is measured to the nearest 0.1 kg by a beam scale with the subject wearing light clothes and without shoes. Height is measured standing, the head in the Frankfurt Plane position. If the participant is unable to stand, height is measured using indirect demi-span methods. Demi-span is the distance from the midline at the sternal notch to the web between the middle and ring fingers along outstretched arm. After that, height is calculated by a standard formula [11].

Concentrations of plasma albumin and prealbumin are measured according to standard protocols at the Eastern Finland Laboratory Centre ISLAB.

Grip strength of both hands is measured using a Saehan dynamometer (Hydraulic Hand Dynamometer, Saehan Corporation, South Korea) in a sitting position and with an elbow in 90° flexion close to the body. Participants are allowed two maximal efforts for both hands, and the mean value per hand is used.

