#### Interview and clinical examination by a dental hygienist

A dental hygienist interviews the participants before carrying out a clinical oral health examination. The interview comprises of questions about the use and opinions of oral health services, self-reported oral health including the need for care, oral health-related quality of life, oral health-related behavior, attitudes towards oral health, and how caregivers assist care recipients in oral care

The dental hygienist conducts clinical examinations using mouth mirrors, WHO periodontal probes, and a headlamp with the participant sitting or lying down [12]. The subjects are first asked about the need for antibiotic prophylaxis in dental care, and if they answer yes, periodontal measurements are excluded. At first, the presence, type, and condition of removable dentures by the jaw are examined outside of the mouth. The need for repair is recorded as yes/no and denture hygiene will be marked as good if no visible plaque or calculus is found. Those wearing removable dentures are asked whether pain exits while using the dentures and if yes what kind of pain. The intraoral examination begins with an examination of the oral mucosa. After that, the number and condition (sound, filled, fractured, decayed, radix, or missing) of the teeth are recorded. The modified Silness and Löe index is used to register plaque [13]. Plaque is measured in the buccal surface of each tooth and registered as no visible plaque, visible plaque in gingival margins, visible plaque also elsewhere and the highest value per tooth is recorded. The number of mobile teeth is recorded after which the periodontal condition of the teeth is examined. Depths of the periodontal pockets are measured on every tooth except wisdom tooth and tooth remnants and registered as no deepened pocket, pocket 4–5 mm, or pocket ≥6 mm. Only the deepest pocket per tooth is recorded. The presence of gingival bleeding on probing is also registered from each tooth except wisdom teeth and recorded as yes, no, or unable to be examined/tooth missing. Possible needs and reasons for acute dental care are recorded, and further instructions to seek care are given to participants.

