### Interventions

#### Nutritional intervention

The tailored nutritional intervention is based on the baseline MNA test and information on plasma albumin concentration and 4-day food records. Based on this evaluation, the nutritionist plans individualized nutritional care together with the FC and possibly also with the CR her/his nurse or relatives, if necessary. The nutritional care plan is developed for those who were at protein-energy malnutrition (PEM) or risk of PEM (MNA score <24 and plasma albumin <36 g/L. Those with insufficient energy or protein intake, or with weight loss, are instructed to increase their intake of energy nutrients by nutrient-dense food items and the number of meals and snacks. To increase energy intake participants are advised to eat more frequent small meals and snacks during the day and to increase the use of vegetable oils in foods and use high-fat vegetable oil-based spreads on bread. To increase protein intake, participants are advised to use dairy products like milk or sour milk as a drink, cheese on bread, and quark, yogurt, curdled milk, and cottage cheese as snacks and to eat daily meals with meat, poultry, fish, or sources of plant protein. The participants are given both daily meals and oral health care written instructions.

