#### Oral health intervention

Based on the dental hygienist interview and the clinical examination, an individually targeted preventive intervention is carried out on those participants in need. The intervention includes at least one of the following verbal and written instructions: teeth brushing, interdental cleaning, cleaning and storing dentures, cleaning of the oral mucosa, dry mouth care, or some other. Intervention instructions are given to the FC.

At the 2-month visit, a nutritionist and a dental hygienist will evaluate the implementation of the nutrition and oral care plans and provide follow-up instructions as needed. Final measurements, the same as at the beginning of the study, will be made at the end of the intervention at 6 months. Follow-up measurements on nutrition and oral health will be made at 12 months. The intervention is terminated if a participant dies or is unable to continue the study due to worsening of his/her condition.

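### One unblinded researcher role both enrols and allocates, and the counselling roles also examine; the reason given for no blinding covers neither allocation nor outcome measurement

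*Protocol article*

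**What the plan says.** **Allocation.** Under Study population, service managers approach caregivers first. Then "the contact details of those interested are communicated to the researchers who are in contact with the volunteers by telephone". The next step is also given to the research side: "The researcher will record the participants, who will be willing to participate in the study and generate the allocation with the computer". No second person is named, and the order of consent, baseline examination and allocation is not fixed.

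**Blinding.** The same section concludes: "So, participants and researchers are not blinded because it is impossible considering the design of the study". The reason given is that the intervention concerns nutrition and oral health. The Discussion lists the lack of blinding as a limitation, again attributing it to the design.

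**Who measures and who counsels.**
- Nutrition: MNA, weight, height and grip strength stand under the heading "Interview and clinical examination by a clinical nutritionist". Under Nutritional intervention, "the nutritionist plans individualized nutritional care together with the FC".
- Oral health: "The dental hygienist conducts clinical examinations using mouth mirrors, WHO periodontal probes, and a headlamp", and that examination includes the plaque score. Under Oral health intervention, "Based on the dental hygienist interview and the clinical examination, an individually targeted preventive intervention is carried out".
- At 2 months, "a nutritionist and a dental hygienist will evaluate the implementation of the nutrition and oral care plans" and give further instructions where needed.
- The 6-month measurements are described as the same as those at the start. No other examiner is named for 6 or 12 months.

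**What is protected.** Albumin and prealbumin are measured at an external laboratory. Albumin and plaque are the two criteria on which the sample size rests.

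**The concern.** The article treats three separate matters as one. Participants and counsellors cannot be masked to counselling, and that is accepted. Concealing the next assignment from the person who enrols is possible in any open trial. Keeping the group from the person who measures is often possible, if imperfectly. The reason given addresses only the first matter, yet it is applied to all researchers.

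Two biases are then at stake. If the person who telephones and lists volunteers can know or influence the next assignment, the arms may differ in prognosis from the start. If the person who counselled a household later grades its plaque or administers its MNA, expectation can tilt the score towards the counselled group. Plaque is graded by eye into three levels, and the MNA contains judged and self-assessed items. Both belong to the nutritional and oral health status that the Abstract names as primary.

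**Working it through.** **1. Roles side by side (Protocol article)**

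| Task | Role named | Section |
|---|---|---|
| Telephone contact with volunteers | Researchers | Study population |
| Recording the willing | The researcher | Study population |
| Generating the allocation | The researcher | Study population |
| MNA, weight, grip strength | Clinical nutritionist | Interview and clinical examination by a clinical nutritionist |
| Nutritional care plan | Nutritionist | Nutritional intervention |
| Plaque, pockets, bleeding | Dental hygienist | Interview and clinical examination by a dental hygienist |
| Oral counselling | Provider not named; based on the hygienist's interview and examination | Oral health intervention |
| 2-month review of plans | Nutritionist and dental hygienist | Oral health intervention |
| Albumin, prealbumin | External laboratory | Interview and clinical examination by a clinical nutritionist |
| Background data at baseline, 6 and 12 months | Trained nurse | Background variables |

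The overlap of roles is in the text. That the same individuals examine at follow-up is an inference from it.

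**2. Does the planned analysis remove the bias?** Statistical analyses plans generalized linear models with baseline data as covariates and group as fixed factor. Let the true effect be τ and the differential scoring at follow-up be b. In the linear case:

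observed outcome = α + β × baseline + (τ + b) × group + error

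The group coefficient estimates τ + b, so baseline adjustment leaves b untouched. For selection, adjustment helps only to the extent that the measured covariates carry the imbalance.

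**3. The article's own figure.** It gives 60 per subgroup, power 0.80 and α 0.05, but no effect size, SD or sidedness, so 60 cannot be reproduced forwards. Solved backwards (two-sided, normal approximation):

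d = √(2/60) × (1.960 + 0.842) = 0.1826 × 2.802 = 0.51 SD

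One-sided, the same calculation gives 0.45 SD. The point does not depend on this figure; it only supplies a scale.

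**4. Illustrative size of detection bias.** The documents give no scoring shift, so b = 0.1 and 0.2 SD are assumed. Against 0.51 SD these are about 20% and 39% of the detectable difference. With no true effect, the two-sided rejection probability is

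P = 1 − Φ(1.96 − λ) + Φ(−1.96 − λ), with λ = b / √(2/n)

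| n per group | b (SD) | λ | P |
|---|---|---|---|
| 60 | 0 | 0 | 5.0% |
| 60 | 0.1 | 0.1/0.1826 = 0.55 | 8.5% |
| 60 | 0.2 | 0.2/0.1826 = 1.10 | 19.5% |
| 125 | 0.1 | 0.1/0.1265 = 0.79 | 12.4% |
| 125 | 0.2 | 0.2/0.1265 = 1.58 | 35.3% |

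The 125 assumes that the 250 caregivers are split 1:1. The article gives no ratio, and it speaks of intervention groups in the Abstract but of one intervention group under Study design. Hence both sample sizes are shown.

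**The case against.** **Concealment is not shown to have failed.** Read in order, the text has willingness recorded before the allocation is generated by computer. If all volunteers were listed first, there would be little room for selection. A condensed article also commonly leaves concealment mechanics to the full protocol. Both points stand. A reader might infer that the researcher knew the next assignment and that selection bias is therefore present; the text does not support that. What remains is what the article does state: one unblinded role enrols and allocates, and the reason offered for the lack of blinding has no bearing on that arrangement.

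**Self-scoring is partly inferred.** The examining team is named only for baseline. The wording on the 6-month visit describes the measurements, not the examiners, and the initial oral counselling is described without naming who gives it. So it would go too far to treat it as established that each counsellor scores the people he or she counselled. The overlap by role, with no other examiner named, is enough for a risk.

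**The limitation is disclosed, and one main criterion is safe.** The Discussion admits the lack of blinding, but with the same over-broad reason. Albumin comes from an external laboratory and is largely outside scorer bias. The detection concern therefore does not reach every main criterion.

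**Masking would be imperfect.** Participants know their group and may reveal it, particularly during dietary questions at home, and they answer the self-assessed MNA items themselves. A hygienist who did the 2-month review cannot be masked at 6 months. This limits what any remedy can achieve; it does not make the attempt impossible.

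**Conclusion.** The point holds as a risk that the article fixes badly, not as demonstrated bias. One unblinded researcher role has both enrolment and allocation, with neither separation nor order set. Blinding is called impossible for all researchers on a ground that covers only participants and counsellors. Examination and counselling sit in the same two roles.

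The outcomes exposed to scoring are plaque, the other examiner-scored oral measures, MNA and grip strength. Albumin is largely protected.

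The rates of about 8.5% to 19.5% (60 per group) and 12% to 35% (125 per arm) show how sensitive a 5% test is to a small tilt in scoring. They should not be read as this trial's error rate. They rest on the assumed shifts, a two-sided test, a normal approximation, independent observations and, for the larger figure, an assumed 1:1 split. Selection bias is not quantified, because the documents offer nothing to quantify it with. The change is worth making because it is cheap, not because the trial is shown to be invalid.

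**What to change.** 1. **Allocation.** For caregiver and recipient pairs not yet allocated, have a team member who does not enrol generate the list. Release each pair's assignment only after consent and the completed baseline examination. This assumes that a pair is allocated together; the article should say so. Releasing it after baseline also protects the baseline values used as covariates.
2. **Wording.** Limit the statement that blinding is impossible to participants and counsellors, under Study population and in the Discussion.
3. **Nutrition measurements.** Have the trained nurse, who already collects data at 6 and 12 months, administer the MNA, weight and grip strength without being told the allocation. In Table 1 grip strength is scheduled only to 6 months. Accept that some participants will reveal their group.
4. **Plaque.** Keep the examination order already described, and score without sight of earlier charts or the care plan. This reduces the bias but does not mask a hygienist who did the 2-month review.
5. **Reporting.** Label plaque, and any MNA scored by a counsellor, as unmasked. Name albumin as the outcome least exposed to scorer bias.

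The cost is a short procedure note and a shift of tasks within roles already on the team. The documents give no workloads, so the nurse's capacity needs checking. Scheduling becomes less flexible. Because Trial status says recruitment is under way, this is a mid-trial change: its date must be documented, and it cannot help pairs already allocated, except at their remaining follow-up visits.
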